### Providing data

#### Anonymised deidentified data

Data sets should be anonymised (that is, have all directly identifiable material removed, such as name, address, postal code, record number). A patient identification number should be provided to facilitate communication and data queries. For the purposes of this report, the age of the patient (an indirect identifier) is essential and should be provided [57].

#### Data format

The data will be accepted by the PICNICC Collaborative in any electronic format, but ideally a 'flat' spreadsheet format (such as Microsoft Excel; Microsoft Corp, Redmond, WA, USA) will be most useful, with one episode per row and variables listed in columns. Each patient should be assigned an in-cohort unique identifier (such as a simple number 1, 2 ... *n*) to highlight repeated episodes in the same patient. A suggestion for coding the variables is provided in Appendix 4 in Additional file 4 and a sample flat file is available on request.

#### Transfer of data

The data should be transferred to a secure password-protected web server or by pretty good privacy-encrypted email. This permits a secure and identifiable connection to the University of York servers and minimises the possibility of data loss.

#### Data checking

Simple checks of data integrity will be undertaken prior to analysis. These checks will include sense checking of data (for example, impossibly low presenting temperatures, such as less than 30°C or for second episodes of FNP where the outcome of the first was death), clarifying missing data (that is, ensuring missing data is recorded as 'missing' rather than 'zero') and calculating simple descriptive statistics of 'essential' elements to assess for 'outlier' studies (for example, age, sex, number of episodes per person). Any problems or inconsistencies flagged during these procedures will be discussed with the individual responsible for each study and amended as appropriate by consensus.

### Ethical and regulatory considerations

This IPD protocol has been approved in the United Kingdom by the University of York Health Services Research Ethics and Research Governance Committee. Each clinician member of the PICNICC Collaborative is advised to seek country-specific advice regarding the regulations which apply to data shared in this study.

### Plan of investigation

#### Method of analysis

The primary method of analysis for the PICNICC study will be the use of multivariable logistic regression modelling. There are a series of different analytical techniques that can be used to produce rules, including multivariable regression analysis, classification and regression tree (CART) models, discriminant analysis and neural networks. There is no clear evidence that one method is superior to any other [58], and, as multivariable logistic models have the widest clinical understanding and applicability, this method has been selected.

In the primary analysis, data used will be from the first recorded episode for each patient to predict an absence of adverse outcomes due to the individual episode (that is, death, intensive care requirement, medical complication, bacteraemia or other significant bacterial infection). Following the primary analysis, outcome data and predictor variables from subsequent episodes will be analysed to assess the independence or otherwise of these data, and this information will also be included using an appropriate model.

Prospective and retrospective cohorts will be considered separately in the initial analyses on the basis of the hypothesis that there will be a clinically important difference between the two types of studies. If no difference is found, then the data set will be examined as a whole. The prognostic importance of individual variables, both unadjusted and adjusted for other variables (the latter to summarise independent prognostic value), will be summarised for each study.

### Assessment of study and data quality

There is very little advice in the literature for assessing the quality of prognostic studies. Altman and Lyman presented suitable criteria that those initiating a primary prognostic study should consider [59], and they suggested that every effort should be made to limit potential biases and to emulate the design standards of a clinical trial. Ideally, the data should be collected prospectively, with little missing data for predictors or outcomes and with predefined hypothesises. We will use these guidelines and those published by Hayden *et al. *[60] to help inform the quality of the IPD obtained. For example, an assessment will be made of the proportion of missing data and the completeness of follow-up. The influence of any studies considered problematic (for example, those with large amounts of missing data or a great deal of incomplete follow-up) on the prediction model will then be considered, resulting in either their exclusion or in sensitivity analyses comparing model estimates when they are included or excluded.

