In the Predicting Infectious Complications of Neutropenic sepsis In Children with Cancer (PICNICC) study, the collection and analysis of IPD will provide specific benefits that overcome many of the problems found in the aggregate data meta-analysis. Many of the benefits of IPD analysis are technical, being related to the statistical methods underlying the meta-analysis and the building of predictive models. Although at first sight the failure to address the problems inherent in statistical interpretation may seem to be clinically irrelevant, it has clear and real clinical implications [33]. Other benefits are more obviously clinical; for example, the collection of the different data sets will enable us to clarify and harmonise the different outcomes collected.

One of the primary 'statistical' benefits will be the use of firmly prespecified potential predictor variables built upon the experience of the PICNICC Collaborative and the systematic reviews. This will guard against the development of purely data-driven analyses, which have a tendency to overestimate any predictive value [28].

In the reviews, we found the studies designed to build a CDR used a large number of variables (median = 13, range = 2 to 39) and had a small number of events (median = 36, range = 4 to 178) with 70% (12 of 16) studies having fewer than 10 events per variable under consideration and no study having more than 14 events per variable. These low event-per-variable ratios render predictive conclusions drawn from the studies unstable and estimates of predictive power overly optimistic [34]. IPD will allow us to consolidate the information and increase greatly the number of events studied from the same number of predictive variables.

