#### Inclusion and exclusion criteria

Studies will be considered for inclusion in the IPD meta-analysis if they are cohort studies of children and young people presenting with FNP and/or with either prospective or retrospective data collection, including RCT data; if they provide data for all 'essential' predictive variables in more than 50% of included episodes (see 'Core data set and variables' section); and if they provide details of two or more study-defined outcomes in more than 90% of individual episodes of FNP.

Studies will be excluded if they are case series (for example, studies of only 'Gram-negative bacteraemias') and if they did not record data on all 'essential' predictive variables or cannot provide sufficient outcome data.

Studies will be included if they focus on the collection of data from children and young people (between 0 and 24 years old). The purpose of the inclusion criterion of studies of young people up to the age of 24 years is to address a paucity of research on individuals in the 'young adult' age range [54]. Data from individual patients ages 25 years and older will be excluded from this analysis. The median age of inclusion in the 'children's' cohorts examined in our reviews was about 7 years old (ranging from 1 month to 23 years), and the 'adult' study from the Multinational Association for Supportive Care in Cancer group [55,56] has a median age of 52 years (range, 16 to 91 years old).

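### A study flagged as problematic may be excluded as a result of considering its influence on the prediction model, so the development data set can depend on the results

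*Protocol article*

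**What the plan says.** The section Assessment of study and data quality sets out a sequence. Published guidelines are used "to help inform the quality of the IPD obtained", for example through the proportion of missing data and the completeness of follow-up. Problematic studies are illustrated as "those with large amounts of missing data or a great deal of incomplete follow-up". Then comes the step at issue: "The influence of any studies considered problematic" (the examples follow in brackets) on the model is considered next, "resulting in either their exclusion or in sensitivity analyses comparing model estimates when they are included or excluded".

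Three other places bear on this:

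- Inclusion and exclusion criteria already screens studies for completeness. They enter "if they provide data for all 'essential' predictive variables in more than 50% of included episodes" and "if they provide details of two or more study-defined outcomes in more than 90% of individual episodes of FNP".
- Model development and Assessing model performance plan bootstrapping, shrinkage and leave-one-study-out validation against overoptimism.
- Rationale for an individual participant data analysis lists, as the last of eight benefits, internal cross-validation as protection against data-driven overstatement of predictive power.

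**The concern.** The article offers two outcomes, exclusion or a sensitivity analysis, and places both after the study's influence on the model has been considered. The choice of development data can then depend on the result. If a study that weakens discrimination is more likely to be dropped than one that strengthens it, the reported accuracy is too high.

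The planned corrections deal with overoptimism from fitting and validating in the same data. Nothing says that the exclusion step is repeated inside them. A study that has been removed can never be the one left out in cross-validation, so the model is not tested on it. This matters because the decision rule is meant to identify children who might receive less intensive antibiotic therapy, and because the article criticises existing rules for lacking extensive geographical and temporal validation.

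**Working it through.** The article gives no figure on this point, so there is none to reproduce. The check has two parts.

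**Text.** The order is: assess quality, flag, consider influence on the model, then exclude or run a sensitivity analysis. Exclusion is worded as a result of considering influence. No rule separates the two outcomes, and the sentence does not require both sets of results to be shown if a study is excluded.

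**Size.** From the article: 23 data sets (Status of the project). Assumed: 150 first episodes per data set; about 25% adverse outcomes; one predictor with mean log-odds slope 0.8 (AUC about 0.70); between-study SD of the slope 0, 0.3 or 0.5; and k = 3, 6 or 10 studies flagged independently of performance. Each setting had 400 replicates. Three rules were compared: keep all flagged studies, drop all of them, or drop a flagged study only if leaving it out raises the pooled AUC. The third is a worst case, not something the article states.

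| Slope SD | k | Keep all | Drop all flagged | Drop if AUC rises | Mean inflation | Mean number dropped |
|---|---|---|---|---|---|---|
| 0 | 3 | 0.7043 | 0.7042 | 0.7070 | 0.0027 | 1.5 |
| 0 | 6 | 0.7043 | 0.7037 | 0.7097 | 0.0054 | 2.9 |
| 0 | 10 | 0.7031 | 0.7023 | 0.7134 | 0.0103 | 4.9 |
| 0.3 | 3 | 0.7007 | 0.7009 | 0.7053 | 0.0046 | 1.5 |
| 0.3 | 6 | 0.6998 | 0.7002 | 0.7094 | 0.0096 | 2.9 |
| 0.3 | 10 | 0.7003 | 0.7004 | 0.7172 | 0.0170 | 4.8 |
| 0.5 | 3 | 0.6944 | 0.6939 | 0.7004 | 0.0060 | 1.3 |
| 0.5 | 6 | 0.6924 | 0.6926 | 0.7061 | 0.0137 | 2.8 |
| 0.5 | 10 | 0.6952 | 0.6945 | 0.7188 | 0.0237 | 4.6 |

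Keep-all and drop-all differ by at most 0.0008. A rule fixed beforehand therefore produces no systematic inflation here, whichever way it goes. The inflation comes from choosing after the effect is seen.

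A hand check for slope SD 0: treat the pooled AUC as an equal-weight mean of 23 study AUCs. Its SD is about 0.0054 / 0.52 = 0.0104, where 0.52 is the inflation in SDs for k = 6. One study's AUC then has SD about 0.0104 × √23 = 0.050. Dropping a study only when it lies below average gains about 0.399 × 0.050 / 23 = 0.00087 per flagged study. For k = 3, 6 and 10 this gives 0.0026, 0.0052 and 0.0087. The value for k = 10 is a little low because removing several studies raises the weight of those that remain.

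Two further simulations assumed 23 studies of 40 to 300 children and flagged studies that do not truly differ. One gave mean rises of 0.0047, 0.0080 and 0.0116 for 4, 6 and 8 flagged studies (95th percentiles 0.0122, 0.0184 and 0.0241). The other gave 0.002, 0.003, 0.006 and 0.008 for 2, 4, 6 and 8 flagged; with slope SD 0.3 it gave 0.003 to 0.013. In the latter, the 95% confidence half-width of the pooled AUC was about 0.020.

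**The case against.** The strongest reply is that flagging is by quality. Only studies found wanting on missing data or follow-up reach the influence step, and nothing says that a study is dropped for fitting poorly or to raise the AUC. That stands: it limits the freedom to flagged studies and makes the simulated dropping rule a worst case. It does not change the order of the sentence, in which exclusion follows from considering influence.

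A reader might infer that the plan contradicts its statement "This will guard against the development of purely data-driven analyses, which have a tendency to overestimate any predictive value". It does not. There, the safeguard is the prespecification of candidate predictors, not the choice of studies. What remains is a tension with the general aim of avoiding data-driven overstatement of predictive power.

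A reader might also infer that dropping studies would narrow the confidence intervals. This is not supported: in the one simulation that looked at it, the standard error of the pooled AUC rose by 2% to 10%, because patients are lost.

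It may be said that the entry criteria make later quality assessment unnecessary. They do not. A study can enter with essential predictors missing in almost half of its episodes, and no limit is set on follow-up, so a later quality step is reasonable.

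Finally, numeric cut-offs for missing data and follow-up can properly sit in a fuller protocol or analysis plan, and their absence from an article is no fault. The point rests on the sequence that the article does state. Study-level summaries, random effects and leave-one-study-out validation give partial protection, but none is said to cover studies already removed.

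**Conclusion.** The point holds in a limited form. The article allows a flagged study to be excluded as a result of considering its influence on the prediction model, and the planned optimism corrections are not said to account for that choice.

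The likely size is small: a mean AUC rise of about 0.002 to 0.012 across the three simulations when flagged studies do not truly differ, and up to 0.024 with strong heterogeneity and 10 of 23 studies flagged. These figures rest on assumed study sizes, event rate, predictor strength and numbers flagged, and on the worst-case dropping rule. They illustrate direction and order of magnitude and do not predict what the analysts would do.

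A reader might conclude that exclusion should be forbidden altogether. The results do not require that, since a drop-all rule fixed in advance was as free of inflation as a keep-all rule. What needs fixing is the timing and the grounds of the decision.

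**What to change.** Replace the sentence so that it says three things:

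- Studies are flagged from missing data, completeness of follow-up and design.
- Whether each flagged study is kept in or excluded from the primary model is decided on those same grounds, and recorded, before any outcome model is fitted.
- Influence on the model is examined only in the sensitivity analyses, with results reported both with and without the flagged studies.

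The simplest version keeps every eligible study in the primary model. The change is timely, since Status of the project reports that analysis has not begun.

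The cost is one sentence, as the sensitivity analyses are already planned. If all studies are kept, the downside is that lower-quality data stay in the primary model, with their effect shown in the sensitivity analysis.

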### Model development

The model will initially incorporate the simplest predictor variables (malignant diagnosis, age, time since chemotherapy, and maximum recorded temperature) before standard additional variables (such as clinical assessments of compromise, inpatient or outpatient status, white blood cell counts or other haematological parameters) are added. Further specialist tests (for example, CRP and IL-6 levels) will be added. The type of antibiotic therapy used will always be incorporated into the model as a categorical variable. Potential sources of heterogeneity (for example, in effects of particular variables across studies) will be incorporated as random effects as appropriate. The models will be assessed for improvement in fit by using an information criterion (for example, Akaike's information criterion) with a *P*-value of < 0.15 used for inclusion. We will use a 15% rather than a 5% level, as we feel this is more conservative and will limit the chance of missing important covariates. At the stage of deciding our final model, however, we will check that the model's predictive accuracy (discriminatory ability) is improved by the inclusion of variables whose significance is between 5% and 15%. If predictive accuracy is not improved, then these variables will be removed.

This approach (of adding specialist tests only after considering the simpler tests) maximises the utility of a model by ensuring that, if extra tests with their additional costs are required, they will add considerable predictive power to existing simpler variables [61]. We will use bootstrapping and shrinkage to adjust for potential overoptimism (bias) in parametric estimates and trends.

Continuous candidate variables will be assessed using the best fitting functional form considering appropriate transformations or fractional polynomials (also assessed using an information criterion) as suggested by previous evidence. Missing data will be examined to define the nature of the 'missingness'. If they are missing at random, then multiple imputation techniques will be used to address these gaps utilising all the other available data [50,51]. The results of these analyses will be compared with a complete case analysis. We will conduct an analysis comparing the new model that we develop with other validated models, for example, that of Santolaya *et al. *[62]. This will provide an opportunity to test these CDRs against data from other geographical areas.

We acknowledge that there may be unforeseen challenges caused by the variations in the data formats available from the different studies. Therefore, we acknowledge that establishing the definitive analysis plan will be an iterative process and may even demand novel methodological developments (see 'Further research opportunities arising from PICNICC' section).

### Assessing model performance

An important goal of a prediction model is to classify patients into risk groups. The developed model will produce a risk score for each individual that is based on the patient's own predictor values. We will then use a cutoff value to decide when a risk score is high (such that we predict an adverse outcome) and when it is low (such that we predict a good outcome); this will be our CDR. The calibration of the model will be assessed by classifying children into deciles ordered by predicted risk and considering the agreement between the mean predicted risk and the observed events in each decile. The derived CDR will be cross-validated by comparing the classification of each patient with his or her actual outcome, thus allowing an estimate of the sensitivity and specificity of the prediction model. Next, by varying the chosen cutoff level, we will be able to produce a receiver operating characteristic curve (ROC) summarising the sensitivity and specificity of the predictive rule across the range of cutoffs. The overall discriminatory ability will be summarised as the area under the ROC (AUC ROC) with the 95% confidence interval. The most suitable cutoff level can then also be detected.

Each predictive model will be tested by checking how it performs against the data from all but one of the studies in turn (cross-validation of intrinsic prognostic performance) [63] and by using the bootstrap procedure [64]. This will adjust for overoptimism in the estimation of model performance due to validation in the same data set that was used to develop the model itself.

The improvement in model performance by adding prognostic factors will be assessed by net reclassification improvement. By analysing the difference among the prognostic factors, a shrinkage factor will be calculated and the model will be corrected by this shrinkage factor. Note also that clustering of patients within studies will be accounted for in the model framework.

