### Systematic reviews of existing knowledge

In preparation for this project, two systematic reviews were undertaken to assess the prior knowledge of the discriminatory ability of CDRs [19] and inflammatory serum markers ([name], [name], [name], [name], [name]) in children and young people with FNP. The systematic review of CDRs initially identified 2,057 potential studies and finally included 24, of which 21 had data in a usable format. It showed that two groups of studies have been undertaken to risk-stratify children who present with FNP. Researchers in the first group of studies examined the use of clinical examinations to predict radiographic pneumonia (4 studies) [20], and investigators in the second group examined more general infectious complications (20 studies) [19].

Among the studies in which general infectious complications were examined, 16 separate models were produced and contained 9 data sets used to validate previously derived models. The researchers studied a variety of outcomes with individual differences in definitions, but covered five main categories: death, critical care requirement, serious medical complications, significant bacterial infections and bacteraemia.

Only one rule could reasonably be assessed across multiple data sets: that of absolute monocyte count and temperature criteria proposed by Rackoff *et al. *[21] to exclude bacteraemia. The most appropriate meta-analysis of the rule's effectiveness led to estimates of moderate discriminatory ability, with the average probability of bacteraemia in the groups being low risk = 6% (95% CrI = 1% to 34%), middle-level risk = 18% (CrI = 3% to 37%) and high risk = 49% (95% CrI = 6 to 84%).

Of the other rules, the model of Santolaya *et al. *[22] showed a good ability to differentiate between low- and high-risk groups when a wider definition of 'serious infection' was used, with average predictive ability estimated as low risk = 13% (95% CI = 9% to 18%) and high risk = 72% (95% CI = 68% to 75%). The rule has been developed and tested in Chile and may be of limited applicability in Western Europe and North America [23]. Other rules show promise and have clinical physiological similarities, but have not undergone extensive testing.

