### Validation in new data

We will compare the predicted and observed event rates to assess calibration (as described above) and the AUC ROC to assess discriminatory ability. If new data become available after the formation of the PICNICC Collaborative, they will provide an excellent test bed for the newly proposed model. Such an analysis is outside the initial scope of this project. We will update the model if it shows poor performance to adjust it to the new situation by recalibration or revision methods, depending on discrimination performance. Simple diagnostic test accuracy measures (such as positive and negative predictive values) will be computed for a hypothetical population (with its particular incidence rates) to aid clinical interpretation of the study results that define a low-risk group.

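### Calibration is checked only by deciles of predicted risk, not study by study, so errors of opposite sign between studies could go unseen

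*Protocol article*

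**What the plan says.** Assessing model performance names one calibration method. Children are grouped by predicted risk ("The calibration of the model will be assessed by classifying children into deciles ordered by predicted risk"), and the check consists of "considering the agreement between the mean predicted risk and the observed events in each decile". Validation in new data carries the same method over ("We will compare the predicted and observed event rates to assess calibration (as described above"), but places that analysis outside the initial scope of the project.

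Three other provisions bear on differences between studies:

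- Cross-validation by study, with the bootstrap: "Each predictive model will be tested by checking how it performs against the data from all but one of the studies in turn". The stated purpose is to adjust for overoptimism. Neither the performance measure nor any reporting by study is named.
- Clustering: "clustering of patients within studies will be accounted for in the model framework".
- Heterogeneity, in Model development: "Potential sources of heterogeneity (for example, in effects of particular variables across studies) will be incorporated as random effects as appropriate".

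Method of analysis adds that "Prospective and retrospective cohorts will be considered separately in the initial analyses", with the whole data set examined together if no difference is found. Status of the project gives 23 data sets from 12 countries and says no analyses have yet been done.

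**The concern.** The purpose of the model is to define a low-risk group who might receive less intensive treatment, and to predict the proportion of events in that group for a later trial. Both uses rest on absolute risk. What a new centre needs to know is whether the predicted low risk holds in a setting like its own.

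A decile table over all children answers a different question: whether predicted and observed risk agree on average across the collection. If a model predicts too high in one study and too low in another, children from both fall into the same decile and the errors offset each other.

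The protocol itself gives reasons to expect baseline risk to differ. Outcome definitions varied in the reviewed studies, a contributing study need supply only two or more outcomes, outcome assessment methods may differ, and a clinically important difference between prospective and retrospective cohorts is hypothesised.

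**Working it through.** The protocol states no calibration figure, so there is nothing to reproduce. The check is of the mechanism.

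**Smallest case.** Two equal studies, each with predicted risk 6% in the low-risk group and true risks of 1% and 11%. The pooled observed risk is (1% + 11%)/2 = 6%, which matches the prediction exactly although neither study does.

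**Simulation inputs.** From the document: 23 data sets. Assumed: 100 or 200 children per study; one standard normal predictor x; true model logit(p) = -1.3 + x + u, where u is the study's intercept deviation, normal with mean 0 and SD 0, 0.3, 0.5 or 1.0; low risk defined as predicted risk below 10%. The 10% is illustrative and is not proposed as a threshold. One logistic model without study terms was fitted to all children, with 200 runs per setting.

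**Quantities.**
- Decile gap: the absolute difference between mean predicted and observed risk in a decile; the largest of the ten is taken, then averaged over runs.
- O/E by study: observed events divided by the sum of predicted risks; 5th to 95th percentile across studies.
- True low-risk event rate by study: the mean true risk of children predicted below 10%; 5th to 95th percentile across studies.
- Held-out gap: the largest decile gap when each study is predicted from the others and the held-out predictions are then pooled (20 runs).

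**Results at 200 children per study.**

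| Intercept SD | Largest decile gap (points) | Held-out gap, pooled (points) | O/E by study | Low-risk group, pooled: observed / predicted | True low-risk rate by study |
|---|---|---|---|---|---|
| 0 | 3.1 | 3.2 | 0.84-1.16 | 6.5% / 6.5% | 5.9-7.0% |
| 0.3 | 3.2 | 3.3 | 0.69-1.34 | 6.6% / 6.6% | 4.2-9.5% |
| 0.5 | 3.1 | 2.8 | 0.57-1.51 | 6.7% / 6.7% | 3.1-11.7% |
| 1.0 | 3.3 | 3.8 | 0.30-1.93 | 6.7% / 7.2% | 1.2-18.2% |

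At 100 children per study the decile gap was 4.3 to 4.7 points, again with no trend in the SD, and the low-risk ranges were almost the same. Across all settings the Hosmer-Lemeshow statistic averaged 7.3 to 8.1 and rejected in 1% to 7% of runs. The decile comparison therefore gave no signal at any level of heterogeneity. Holding studies out did not help when the held-out predictions were put back into one decile table.

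**How plausible are these SDs?** Systematic reviews of existing knowledge gives two low-risk figures. For the monocyte-and-temperature rule it reports "low risk = 6% (95% CrI = 1% to 34" per cent. Read as between-study spread, that is (logit 0.34 - logit 0.01)/(2 × 1.96) = (-0.663 + 4.595)/3.92 = 1.00. For the Chilean rule it reports 13% with an interval of 9% to 18%, which on the same reading is (-1.516 + 2.314)/3.92 = 0.20. Neither interval is stated to be between-study spread, so these two values only suggest a range to try.

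**The case against.** The strongest case against is that a cross-study check is already in the plan. Calibration is one of the performance aspects in the same section, so the leave-one-study-out loop may be meant to cover it. It would then be wrong to infer that the plan ignores differences between studies. That stands. What remains is that the text gives the loop a different purpose and does not say that calibration will be looked at in each left-out study. Pooling the held-out predictions would still hide the problem.

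Other stronger readings also go beyond the document:

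- A reader might take it as stated that the deciles are formed over all studies. It is not written; it is the natural reading because no stratification is given. Prospective and retrospective cohorts are at first kept apart.
- A reader might conclude that predicted and observed totals must agree by construction. That is true of an unshrunken pooled maximum-likelihood fit. The plan includes shrinkage and, as appropriate, random effects, and the simulation had neither. Random effects still do not turn the decile check into a check by study, and a new hospital's intercept is unknown.
- A reader might take the 1% to 34% interval as proof of severe heterogeneity. It is a credible interval for the average probability of bacteraemia under a different rule, and the Chilean rule's interval is far narrower.

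It can also be said that this is a condensed article and that calibration statistics are commonly left to the analysis plan; Model development ends by calling the definitive plan iterative. That holds for the exact choice of statistics. But the article does name a calibration method, and that method cannot show this failure. The remark about iteration concerns variations in data formats.

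**Conclusion.** The point holds as a limitation of the named method. Decile calibration without stratification by study cannot show errors of opposite sign between studies, and no stated analysis would report whether the predicted low risk holds study by study.

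The size is conditional. The document fixes neither the between-study SD of baseline risk nor the study sizes. At an SD of 0.3 the consequence is modest (true low-risk rates of about 4-10%); at 1.0 it is serious (about 1-18%). It does not follow that the model will be badly miscalibrated, or that the decile table will look perfect. The model may be well calibrated on average over the collection, and shrinkage may itself move the decile gaps. The change is worth making because it is cheap and, with new-data validation outside the initial scope, the contributed studies are the main evidence on whether the risks carry over to other settings.

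**What to change.** Within the leave-one-study-out loop already planned, report for each held-out study:

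- the observed/expected ratio, or calibration-in-the-large;
- the calibration slope;
- the observed event rate among children the model places in the low-risk group.

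Summarise each by random-effects meta-analysis with a prediction interval. The meta-analysis is needed because chance alone spreads the study ratios: with no heterogeneity at all they ran from 0.84 to 1.16 at 200 children per study and from 0.78 to 1.23 at 100. Keep the decile table as a descriptive display.

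The cost is a sentence or two of text and a little more analysis. Small studies will give wide intervals, and calibration will probably look less favourable than in the decile table. As no analyses had been undertaken when the article was written, this could still be prespecified at that stage.
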